### **Secondary outcome measures**

#### *PFM strength*

The PFM strength will be evaluated by subjective (vaginal palpation) and objective (manometer) measurements. During the assessments, each participant will be examined in the lithotomy position with an empty bladder and the head of the bed inclined at a 30° angle. The subjective

PFM strength will be measured by digital vaginal palpation based on the modified Oxford grading scale (MOS). Patients will be asked to perform a maximum contraction of the muscles to squeeze and lift against the resistance provided by the assessors' fingers in the vagina. The subjective PFM strength will be classified within the range of Grades 0-5, with higher grades reflecting better strength (0 (no contraction), 1 (flicker contraction), 2 (weak contraction), 3 (moderate contraction), 4 (good contraction), 5 (strong contraction)).

The objective PFM strength will be defined as the maximum voluntary contraction pressure (MVCP), which is referred to as the force-generating capacity of a muscle and evaluated through an intra-vaginal manometer (a vaginal balloon probe filled with 20 ml gas) connected to a PHENIX USB 8 neuromuscular stimulation therapy system, which is equal to a high-precision pressure transducer (Electronic Concept Lignon Innovation, Montpellier, France). MVCP will be calculated as the difference between the vaginal resting pressure (VRP) and its peak pressure during a maximum voluntary contraction. The patients will be asked to perform maximum contractions of the PFMs three times without using the abdominal, gluteal, or hip adductor muscles during the contractions. Each contraction will have an interval of 15 seconds. The outcome will be recorded as the average of three measurements. Higher pressure is related to greater strength.

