#### *Patient adherence to treatment*

There is no universally accepted standard for adherence. In our study, patients' adherence to treatment will be determined as the frequency of exercises anticipated for 3 months of supervised treatment, which will be subjectively self-reported and objectively device-recorded. Patients' overall adherence will be categorized as follows:  $50\% \leq$  low adherence;  $50\% - 75\%$  = medium adherence; and  $\geq 75\%$  = high adherence.

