#### **Statistical analysis**

The primary outcome of this study is the ICIQ-UI SF score. An ICIQ-UI SF minimal clinically important difference of 2.5 points was reported by Nyström E in 2015. We referred to two RCT studies reporting ICIQ-UI SF data as the primary outcome for women with SUI with 5-month and 6-month follow-up indicated an assumed standard deviation (SD) of 5. Another study determined a SD of 10 because they expected that the SD at the 24-month time point could possibly be as high as 10. According to our study design, it would be reasonable for us to expect a SD of 8.1 at the 12-month time point. On this basis, the sample-size calculation in our study is expected to be based on a significant difference of 2.5 points in ICIQ-UI SF scores (SD of 8.1) as the primary outcome between the groups. A sample size of 222 participants per group will detect this difference calculated through PASS 15, with a power of 0.9 and a two-sided significance level of 0.05. Thus, a total of 500 women will be recruited (250 women per group), allowing for approximately 10% loss to follow-up during the 12-month period.

The data will be analysed by SPSS version 26.0 (IBM, Armonk, New York, USA). Continuous variables conforming to a normal distribution are presented as the means  $\pm$  standard deviations (SDs), within-group comparisons will be analyzed with paired-samples t tests, and two independent samples t tests will be used for between-group comparisons. If the data is nonnormally distributed and presented as medians and interquartile ranges, the Wilcoxon signed rank test will be used for analyses within the groups, and the Mann-Whitney U test will be used for comparisons between two groups. Categorical variables are presented as n (%), the chi-square test will be used for within-group comparisons, and Fisher's precision probability test will be used for between-group comparisons. The relationship between self-reported

211 adherence and device-reported adherence will be assessed using a scatter plot.  $P < 0.05$  will be  
212 considered significant.

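### The only between-group test given for categorical variables ignores order, although the Oxford grade and the adherence classes are ordered

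*Protocol*

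**What the plan says.** The protocol's Statistical analysis section sets two between-group routes.

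- Continuous variables get a t test. If they are non-normal and summarised by medians and quartiles, "the Mann-Whitney U test will be used for comparisons between two groups".
- Categorical variables are shown as counts and percentages, and "Fisher's precision probability test will be used for between-group comparisons". Within groups they get a chi-square test.

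There is no third route for ordered categories. Two secondary outcomes are ordered:

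- Under PFM strength: "The subjective PFM strength will be classified within the range of Grades 0-5, with higher grades reflecting better strength". This is the modified Oxford scale, assessed by palpation at baseline and 3 months.
- Under Patient adherence to treatment: "Patients' overall adherence will be categorized as follows", followed by low, medium and high classes.

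Neither outcome is assigned a test by name. The only adherence analysis that is named is a scatter plot of self-reported against device-recorded values. The protocol gives no expected distribution, effect size or power for either outcome.

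**The concern.** The question for the Oxford grade has a direction: do women in the device group reach higher grades? Fisher's test on a 2 × k table (the Fisher-Freeman-Halton form) asks a different one: do the two grade distributions differ in any way? It treats the grades as interchangeable labels.

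Two consequences follow if it is the test used. A real, consistent upward shift is missed more often than necessary, because the test spreads its sensitivity over up to 5 degrees of freedom instead of concentrating it on one. A difference in spread with no net shift can also give P < 0.05, and the P value alone does not tell the reader which of the two occurred.

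The wording leaves a choice as well. One analyst may treat the Oxford grade as categorical and use Fisher's test, another may treat it as a non-normal score and use Mann-Whitney. The two can give different P values, and P < 0.05 is the only criterion stated.

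**Working it through.** **1. The plan's own figure.** Inputs from the Statistical analysis section: "a significant difference of 2.5 points in ICIQ-UI SF scores (SD of 8.1"), "with a power of 0.9 and a two-sided significance level of 0.05". By normal approximation, n = 2 × (1.960 + 1.282)² × 8.1² / 2.5² = 2 × 10.51 × 65.61 / 6.25 ≈ 220.6, so 221 per group. The noncentral t distribution gives power 0.8993 at 221 and 0.9006 at 222, so the plan's 222 reproduces. Allowing for 10% loss, 222 / 0.9 = 246.7, or 247, which the plan rounds up to 250. I use 222 analysed women per group below. It was derived for the primary outcome only.

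**2. Why order is ignored.** Let category j hold a_j women in one group and t_j in both, with n₁ women in the first group and N in total. Given the margins, the probability of the table is ∏ C(t_j, a_j) / C(N, n₁). A product does not depend on the order of its terms, so relabelling the grades leaves the P value unchanged. Mann-Whitney uses the sum of midranks, which does depend on the order.

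**3. Analytic size.** Hold the noncentrality fixed and compare a 1-df ordered test with a k − 1 df test. For 80% power on 1 df the noncentrality is (1.960 + 0.842)² ≈ 7.85; for 90% it is (1.960 + 1.282)² ≈ 10.51.

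| 1-df power | 2 df (3 classes) | 4 df (5 grades) | 5 df (6 grades) |
|---|---|---|---|
| 80% | 71% | 60% | 56% |
| 90% | 84% | 74% | 70% |

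**4. Simulation of a consistent shift.** 222 per group, two-sided 0.05, 1,500 trials per scenario, proportional-odds shift, Fisher-Freeman-Halton with 1,000 conditional draws per trial against tie-corrected Mann-Whitney. The Monte Carlo standard error is at most √(0.5 × 0.5 / 1,500) ≈ 1.3 points per power figure. The control distributions are assumptions. For grades 0 to 5, in %: 2/10/28/35/20/5; 3/22/40/25/8/2; 0/3/12/30/35/20; 10/18/22/22/18/10. For adherence: 30/30/40, 20/30/50, 50/30/20. Ranges are over these distributions.

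| Outcome | Odds ratio | Mann-Whitney power, % | Fisher power, % | Loss, points |
|---|---|---|---|---|
| Oxford | 1.4 | 50.3–53.0 | 26.7–31.9 | 19–25 |
| Oxford | 1.6 | 76.3–79.9 | 51.2–54.3 | 22–27 |
| Oxford | 1.8 | 92.5–93.8 | 74.8–78.5 | 15–18 |
| Oxford | 2.0 | 98.1–98.5 | 87.1–91.4 | 7–11 |
| Adherence | 1.4 | 45.5–49.4 | 35.9–39.7 | about 10 |
| Adherence | 1.6 | 72.6–76.3 | 62.8–66.0 | about 10 |
| Adherence | 1.8 | 87.7–91.9 | 80.6–85.6 | 6–7 |
| Adherence | 2.0 | 96.1–97.1 | 92.2–94.5 | 3–4 |

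With no difference (odds ratio 1), Mann-Whitney rejects in 4.0–5.5% and Fisher in 4.3–6.0%, so both hold their size.

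**5. A second model.** Five used grades cut from a latent normal (7/24/38/24/7%, assumed) with a shift of 0.28 SD: Fisher 57%, Mann-Whitney 80%. With chi-square as a close stand-in for Fisher: four grades 63% v 77%, five 58% v 79%, six 54% v 78%, three adherence classes 65% v 74%.

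**6. Spread only.** No shift, latent SD 1.25 v 1.0 (assumed): Fisher rejects 57%, Mann-Whitney 6%. With SD 1.15 v 1.0 (chi-square as stand-in): 25% v 5%.

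**The case against.** **No test is assigned by name.** This stands. A reader might infer that the protocol prescribes Fisher's test for the Oxford grade; it does not say so. A 0-to-5 score could be summarised by a median and sent to Mann-Whitney. Against that, the protocol describes the scale as a classification. It also provides a within-group test for categorical variables, which needs a category recorded at both visits. Cure, improvement and adherence class have no baseline value; the Oxford grade has one. It is not the only candidate, since the ICIQ-UI SF severity bands and leakage type also repeat, so this supports the reading without proving it.

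**Mapping outcomes to tests belongs in the SAP.** Partly right: an SAP, not shown here, may settle it. But the protocol does state a general rule for categorical variables, and for ordered ones that rule is a poor choice.

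**Adherence is weak support.** Largely right. No between-group test of adherence class is stated, adherence starts as a frequency that could be compared on the continuous route, and the loss is small.

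**The power loss is not in the documents.** Right. A reader might take a single figure of about 20 points as fact. It is a fair mid-range value for moderate shifts, but it rests on assumed distributions and an assumed consistent shift. Women unable to contract the muscles are excluded, so grade 0 should be rare. The assumed distribution without grade 0 gives the smallest loss at each odds ratio. If the effect is not consistent across grades, the advantage of a rank test can shrink or reverse.

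**A rejection for spread is a true detection.** Right: the distributions do differ, so it is not a false positive, and the counts and percentages would show where. The risk is one of interpretation only.

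**Conclusion.** The point holds as a defect in how ordered secondary outcomes would be analysed under the plain wording. If Fisher's test is used, it disregards the order of the grades and the direction that the protocol itself states. With 222 per group and a consistent shift at odds ratios of 1.4 to 2.0, it may lose roughly 7 to 27 points of power for the Oxford grade and about 3 to 10 for adherence class, if that class is compared between groups at all. The loss is smallest where the effect is large enough for either test to detect it.

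These sizes rest on assumed distributions and a proportional-odds shift. The documents do not support a firm single figure, nor the claim that Fisher's test is fixed for either outcome. The primary ICIQ-UI SF comparison, its sample size and maximum voluntary contraction pressure are untouched, and the type I error of Fisher's test is correct for its own null. The change is worth making, but the trial's main conclusion does not depend on it.

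**What to change.** In the Statistical analysis section, limit Fisher's test between groups to binary and unordered variables, such as cure and improvement. Add that ordered categories (the Oxford grade, and adherence class or any other ordered bands if they are compared between groups) will be compared by tie-corrected Mann-Whitney or a proportional-odds model. Name one of the two for each outcome. Report an effect estimate with a 95% CI: the probability of a higher grade with the former, the common odds ratio with the latter. If an SAP already does this, align the protocol wording with it.

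The cost is a sentence or two. Mann-Whitney is already in the plan, both methods are available in SPSS 26, and no further patients or data are needed. The small downside is less sensitivity to differences in spread, or to shifts that are not consistent across grades. Showing the full grade distribution by group keeps such patterns visible.

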### 213 **Data management**

214 The data management system adopted in this study includes the following: a patient side for  
215 providing PFMT tasks to patients and collecting questionnaire results, side effects and PFMT  
216 data; a physician side for monitoring and managing the PFMT progress of patients; and a  
217 hospital side for managing the operation process and results of the physician side and patient  
218 side within each hospital.
